### Recruitment and procedure

Since the design is non-randomized, patients are consecutively recruited in the participating outpatient clinics. After initial appointments, therapists in the outpatient clinics identify and approach eligible patients based on the inclusion and exclusion criteria. They participate either in the CBASP@YoungAge treatment arm or in the treatment-as-usual control group (TAU). If screening indicates that the patient is eligible for participation and the family consents, complete study information is given to all participants, and written informed consent is obtained from the primary caregiver and participating child or adolescent.

Assessments are at baseline, post-treatment, and 6 months follow-up. During the treatment phase, a quantitative and qualitative orientated therapy process evaluation by therapist, patient, and caregivers is planned for every session, as is a quantitative evaluation of the general health index by patient and caregivers every 5th session. For detailed information on the study procedure, see Fig. 1 and for an overview of the actual study process and timeline Fig. 2.

**Fig. 1 Fig1:**
[figure not shown]
SPIRIT figure, schedule of enrolment, interventions, and assessments of the trial  [57]

**Fig. 2 Fig2:**

Timeline of the study

The psychotherapeutic process is evaluated during treatment by the study therapists. If difficulties arise during treatment, the study therapists contact the study team in the appropriate outpatient clinic. The intervention or follow-up is discontinued if the caregivers or patients withdraw consent or a different treatment becomes necessary. The therapy process is also discontinued if the trial has to be unexpectedly canceled, or if the study coordinator decides it is necessary to discontinue, for example in case of adverse events. The risk management information below provides further information. The date and reason for discontinuation or drop-outs after screening will be documented.

After treatment completion, trained therapists will carry out regular post-assessments who were not involved in the treatment. Participants have to wait for at least 6 weeks before booster sessions are allowed when needed. If follow-up treatment (e.g., for comorbidities) appears to be necessary during booster sessions, that can be implemented as part of regular outpatient treatment, and will be documented (see Fig. 3 for the study flow).

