The cultivating phase of CBASP@YoungAge is based on a modular course and can be personalized by the therapists in the modules’ order and implementation. It focuses on the Kiesler-Circle-Family-Training and situation analysis, as well as on additional symptoms requiring treatment in additional sessions. The Kiesler-Circle-Family-Training aims to change learned interpersonal behaviors. Past experiences are actively targeted with the patient and relevant others. The most important aim of the Kiesler-Circle-Family-Training setup is the enhancement of flexibility in interpersonal behavior with different family members/significant others. Participants are encouraged to distinguish between different positions in the Kiesler-Circle and are further trained in the perception and reflection of their behavior, evaluation of behavior effects and behavior adaptations to successfully master difficult interactions. During this module, caregivers participate in every session. Situation analysis is applied to enhance the patient’s self-efficacy and ability to act in difficult situations with other people. Patients are trained to notice that they can be in charge and actually change difficult situations. They learn how to shape situations differently to achieve new, changed outcomes for themselves.

The consolidation phase focuses on relapse prevention, reviews the therapy, and checks whether previously set goals have been achieved.

CBASP@YoungAge covers 20 to 30 sessions. Frequency is at least once a week and up to three times a week. It is up to the therapist to decide which modules to use and when based on the individual patient and her/his caregivers. After treatment completion, booster sessions can take place.

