#### Treatment-as-usual control group

The TAU control group is implemented in two cooperating outpatient clinics. The responsible therapists are also psychotherapists in training who are under regular case supervision.

Treatment is based on psychotherapy guidelines [63] and current evidence-based practices for the treatment of depression in childhood and adolescence. No further restrictions with respect to duration or length are made. Family involvement is based on the current psychotherapy accounting rules of the German health care system (every 4th session).

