### Outcomes

Assessments are at pre-treatment (T1), post-treatment (T2) and follow-up at 6 months (T3) (see Fig. 1 for overview). Assessments are face-to-face (clinical interview) or paper-pencil questionnaires and filled out by index patients and/or their caregivers/significant others.

Primary outcomes are, first, the feasibility of the CBASP@YoungAge treatment program. This includes both practicability in the outpatient setting for therapists and suitability for patients and family members, primarily measured by continuous process evaluation (therapists, patients, parents), therapist adherence, patient dropout rate, and recruitment rate during the study and treatment. Second, change in depressive symptomatology between pre- and post-assessment is a primary endpoint, with change measured by the clinical interview (child DIPS, parent or child version) and the Mood and Feelings Questionnaire (MFQ).

Secondary outcomes are the interpersonal behavior between caregiver and children (Impact-Message-Inventory for children and adolescents, IMI@YA), the global health of both caregivers and participating children (KIDSCREEN; Positive mental health questionnaire, PMH), parents' mental health (Brief-Symptom-Inventory, BSI), and parenting quality (Parenting Questionnaire, EFB).

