### Statistical analysis

A preliminary analysis of the results after post-assessment is planned. A full analysis will follow the completion of all follow-up assessments. Data will be analyzed based on the Intention-to-treat (ITT) sample and will help inform power calculations for a future CBASP@YoungAge randomized control trial.

Central aspects with regard to feasibility in the analysis are attrition and reasons for drop-out of patients or parents. These aspects will be recorded and analyzed. Recruitment rate is measured by reporting the number and reasons of patients screened for the intervention group who decided against study participation. We also capture the proportion of patients who participate in each arm at pre-, post- and 6-month follow-up assessment. Furthermore, we access the proportion of patients meeting criteria for response and remission based on the Kinder-DIPS at the different time points. With regard to attrition, therapists will assess the number of sessions of the modules, and the session frequency in general and related to the different modules. In addition, we will record each participant’s individual course of therapy in self-reports, and reports from others, as well as any unexpected events in the course of therapy. For participants who withdraw from the study, the researcher will follow-up with either the therapists or participants to document their reason(s) for study withdrawal. We will assess rates and types of missing data, and the proportion of drop-outs at different stages throughout the trial. We will also assess whether any of the measures display floor and/or ceiling effects. Patient adherence to treatment will be indexed by the mean (SD) number of therapy sessions offered and attended, and by calculating the proportion of participants who undergo a minimum adequate dose (eight or more sessions) in each arm. Adherence of protocol by therapists is analyzed descriptively by the proportion of complete adherence checks and the monitoring of individual case and data management in the study routine. Data completeness is reported as proportions of missing values. Due to sample size and this study’s pilot character, the feasibility analysis is mainly based on the intervention group’s process evaluation. First-interim analyses of results are only possible with sufficient post-measurements. Missing values will be integrated in an iterative imputation method based on a random forest model.

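### One rule stops therapy or follow-up when another treatment is needed, and nothing keeps these patients or early leavers in outcome assessment, which undercuts the stated ITT analysis

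*Protocol article*

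**What the plan says.** The stopping rule stands in the protocol article under Recruitment and procedure, in the text below Fig. 2: "The intervention or follow-up is discontinued if the caregivers or patients withdraw consent or a different treatment becomes necessary". What follows for such a patient is administrative: "The date and reason for discontinuation or drop-outs after screening will be documented". The Statistical analysis section adds that withdrawn participants, or their therapists, are contacted to learn the reason.

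The same section says "Data will be analyzed based on the Intention-to-treat (ITT) sample" and "Missing values will be integrated in an iterative imputation method based on a random forest model".

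On timing, the Outcomes section names T1 before treatment, T2 after treatment and T3 as the 6-month follow-up, with no week for T2. The text below Fig. 2 ties T2 to the end of therapy: "After treatment completion, trained therapists will carry out regular post-assessments who were not involved in the treatment". Treatment length is flexible in the intervention arm, "CBASP@YoungAge covers 20 to 30 sessions. Frequency is at least once a week and up to three times a week", and is not capped for TAU: "No further restrictions with respect to duration or length are made".

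Two further places bear on the rule. Adverse events and risk management allows medication as part of usual TAU care, but makes its start in the intervention arm an event to be reported to the study coordinator. The text below Fig. 2 also lets further treatment found necessary during booster sessions go ahead, with documentation.

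**The concern.** An ITT analysis needs outcomes from everyone enrolled, whatever happened to their treatment. A rule that can end observation because the patient needs something else removes outcomes for a reason that is probably linked to how the patient is doing. Imputation then fills those values from patients who did not need another treatment. That is sound only if the observed data explain the missingness, and here the rule itself gives reason to doubt it. A later analysis plan can add sensitivity analyses, but it cannot recover measurements that were never taken.

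What counts as another treatment is not defined, so the rule may also act unevenly between arms: a new prescription is ordinary care in TAU and a reportable event in CBASP@YoungAge.

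At stake are the pre-to-post change in depressive symptoms (a primary endpoint), the expected advantage over TAU, and the attrition and effect estimates meant to inform power for the planned randomised trial.

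**Working it through.** **1. The passages side by side.**

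- Reason for stopping: need for another treatment, or withdrawal of consent.
- What is stopped: the intervention or the follow-up. The sentence does not separate them.
- What is still collected: date and reason. No continued T2 or T3 is stated.
- What the analysis assumes: an ITT sample with gaps filled by random-forest imputation.

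The rule and the analysis fit together only if discontinued patients are still assessed, and the readable text does not say so.

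**2. How many outcomes could be missing.** Participants and sample size gives 44 recruits, 60% retention and 38 completers. These do not agree: 44 × 0.60 = 26.4, whereas 38/44 = 86.4%. That is a separate error. Here it means that the expected loss is either 44 − 26.4 = 17.6 patients (about 9 per arm) or 44 − 38 = 6 (3 per arm). How many of these would be lost through needing another treatment is not given.

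**3. Possible bias between arms (illustration on assumed inputs).** Suppose a share f of each arm is unobserved, is truly D SD worse, and is imputed at the level of the observed patients. Then

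bias = (f₁ − f₀) × D.

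- Equal shares and equal D: 0.
- 4/22 against 1/22, D = 1: (4 − 1)/22 × 1 = 0.136 SD.
- The same split, D = 0.5: 0.068 SD.

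The Background section cites a pooled effect of 0.36 for psychotherapy in this population. Against it these are 0.068/0.36 = 19% and 0.136/0.36 = 38%. The 0.36 is context and not a design input. If the imputation predictors carry part of the deterioration, the bias is smaller. The arm with more unobserved failures looks better than it is.

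**4. Within an arm.** The pre-to-post change is inflated by f × D even when the arms lose equally: for 4/22, by 0.18 SD at D = 1 and 0.09 SD at D = 0.5.

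**5. Spread of T2.** Weeks = sessions ÷ sessions per week. For CBASP@YoungAge the shortest course is 20/3 = 6.7 weeks and the longest 30/1 = 30 weeks. TAU has no stated upper bound. No week is set for T2 in either arm, and the ANCOVA as described has no term for elapsed time.

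**6. Anchor of T3.** Under Trial status, control recruitment ends in December 2022 and the last follow-up falls by the end of July 2023. From 31 December to 31 July is 30.3 weeks. Less 26.1 weeks (6 months), 4.2 weeks remain for treatment, or 8.5 weeks for a patient enrolled on 1 December. Either T3 is not counted from the end of treatment or the timeline does not fit, so the anchor needs stating.

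**The case against.** The sentence is ambiguous. It can mean that whichever phase is running comes to an end, and since treatment arising in booster sessions is allowed, further treatment does not automatically end follow-up. That stands. It is a reason to reconcile the passages, because the text nowhere says which reading applies.

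The article does not ignore attrition. It promises rates and types of missing data, drop-out by stage, reasons for withdrawal, and participation per arm at each assessment. Sensitivity analyses may sit in an analysis plan that is not shown. This also stands, but those steps describe the loss and do not prevent it.

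A reader might infer that treatment failures are removed from the ITT set. They are not: they stay in it through imputed values. A reader might also infer that early leavers can have no T2. The sentence on post-assessment mainly says who assesses, and does not exclude them.

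A reader might further infer that the arms are in fact measured at different times. The rules permit this but do not show it. Both arms could run to similar lengths, the 6.7-week course needs the fewest sessions at the highest frequency throughout, and TAU is tied to guidelines. Figs. 1 and 3 and the Fig. 2 timeline are not available, and an assessment window there would weaken the timing part. End-of-treatment assessment is a defensible choice for individualised therapy.

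The numerical illustration rests on invented splits. Even 0.14 SD is under half the unadjusted standard error of a comparison of 22 with 22, √(2/22) = 0.30 SD. The trial is a non-randomised pilot whose site effects and staggered starts are openly acknowledged. This limits the consequence but does not remove it, since the estimates are meant to guide the next trial.

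**Conclusion.** The point holds in a limited form. One rule covers stopping therapy and stopping follow-up, and no readable passage commits to assessing patients who need another treatment or leave early. Followed literally, it leaves outcome-related gaps that the stated imputation cannot be relied on to repair, which undercuts the ITT analysis. The rule must be reconciled with the provisions on medication by arm and on treatment during booster sessions.

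Size and direction are unknown. The 0.07 to 0.14 SD between arms depends wholly on the assumed 4/22 against 1/22 loss, on a 0.5 to 1 SD deficit, and on imputation recovering none of it. With equal losses of equal severity the between-arm bias is zero, although within-arm change is still inflated.

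Unequal T2 timing is a possibility to measure and report, not a demonstrated bias. It does not justify requiring a new fixed-time primary endpoint. Week 30 plus 6 months for the last control recruits would run to about January 2024, past the planned July 2023 end, and would change the question being asked.

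**What to change.** 1. Split the rule. Leave the clinical reasons for ending therapy as they are. State that outcome assessment ends only when consent to assessment is withdrawn.
2. Collect at least the MFQ at T2 and T3 from every enrolled patient, whatever their treatment status. State when T2 is taken for those who leave therapy early, and from which event T3 is counted.
3. Reconcile the stopping rule with the text on medication by arm and on treatment during booster sessions, so that the documents say consistently what counts as another treatment for the purpose of assessment.
4. Record and report time from T1 to T2 and to T3 by arm, and add a sensitivity ANCOVA adjusted for it. Elapsed time can itself depend on arm and response, so this checks robustness and does not give a corrected estimate.

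The cost is a short amendment, possibly a change to the consent wording so that assessment can continue after therapy stops, and some extra contact and paper questionnaires for patients who have left therapy. Some will still decline, so gaps will shrink but not vanish. The change has to be made while assessments are still running.

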**Fig. 3 Fig3:**
[figure not shown]
Flowchart of the Study design (based on CONSORT)

### Randomization, allocation concealment, and blinding

Assignment to the two study arms is non-randomized and the allocation is not blinded. The pre- and post-assessments will not be blinded, but rather done by trained psychotherapists who are independent and did not provide treatment in either of the study arms to the respective families.

### Trial interventions

#### CBASP@YoungAge intervention

Based on CBASP [35], we designed the modular, individualized treatment program CBASP@YoungAge for children and adolescents that targets depressive symptoms while additionally addressing interactional difficulties with primary caregivers [58]. The treatment program is manualized and generally applicable in other outpatient psychotherapy contexts. CBASP@YoungAge differs from the traditional CBASP approach in several aspects. First, the active involvement of significant primary caregivers in therapy is mandatory. Second, in line with different previous studies, we modified CBASP more than originally intended [47, 59–62]. Third, the treatment approaches are age-adapted. For detailed information about the CBASP@YoungAge intervention, see the treatment manual ([name], [name], [name]: CBASP@YoungAge – Ein Therapiemanual für das ambulante Setting, in preparation). A brief overview is given in Fig. 4 and in the text below.

**Fig. 4 Fig4:**
[figure not shown]
Procedure and structure of the treatment program (CBASP@YoungAge)

CBASP@YoungAge is conceived for three different age groups (10–12, 13–16, 17–21 years) with depressive disorders and resulting interpersonal problems. It consists of nine different modules that combine aspects of cognitive behavioral therapy (CBT) and psychodynamic psychotherapy. Overall, the intervention consists of three treatment modalities. The first is the individual treatment format, where the therapists work with the child or adolescent on their specific issues. Additional individual sessions with the caregivers are also possible. Second, in the joint format the patient and related caregiver share one session where both work individually on the same topic with the therapist. Third, the joint format the patient and the caregiver participate in the therapy session together. In general, the choice of the appropriate format is left to the therapist, as individual structural conditions must also be considered. The treatment manual only makes recommendations.

This structure aims to provide the most individualized and personalized course of treatment possible while supporting the therapist in every variation. To personalize the treatment, therapists have various age-appropriate adaptation options in the material, as well as flexibility in handling the sequence and the modules’ duration.

The therapeutic relationship in CBASP and thus also CBASP@YoungAge is called “Disciplined Personal Involvement” (DPI) [38] and is characterized by an appreciative, open, and authentic basic attitude towards the patient. DPI is a special form of relationship building that includes the therapist’s personal inner world, thinking, emotions, and reactions to the patient’s behavior [58].

The connecting phase focuses on psychoeducation as well as elaborating on the involvement of significant others and the CBASP-specific transference hypothesis. The connecting phase follow a fixed order to establish the therapy basis. During this phase, an individual model of depression within the CBASP@YoungAge therapy-rationale is developed based on the “interpersonal wall” concept. This wall describes metaphorically the difficulty patients have in interacting appropriately with their social environment. We are assuming that, because of previous experiences, youths’ skills and abilities are impaired in relating to significant others or in interpreting the behavior of others accurately. Such (early) relationship difficulties are assumed to result in hopelessness, distrustfulness, helplessness and loneliness, and reduced contact with other people or activities. Overall, the connecting phase focuses on difficult past and present relationship experiences to establish the transference hypothesis as an overall imprint for daily interactions and the current psychotherapeutic work (e.g., “If I open up to someone and share my emotions, that person won't care and won't react, so I keep my feelings to myself and react defensively.”).

The cultivating phase of CBASP@YoungAge is based on a modular course and can be personalized by the therapists in the modules’ order and implementation. It focuses on the Kiesler-Circle-Family-Training and situation analysis, as well as on additional symptoms requiring treatment in additional sessions. The Kiesler-Circle-Family-Training aims to change learned interpersonal behaviors. Past experiences are actively targeted with the patient and relevant others. The most important aim of the Kiesler-Circle-Family-Training setup is the enhancement of flexibility in interpersonal behavior with different family members/significant others. Participants are encouraged to distinguish between different positions in the Kiesler-Circle and are further trained in the perception and reflection of their behavior, evaluation of behavior effects and behavior adaptations to successfully master difficult interactions. During this module, caregivers participate in every session. Situation analysis is applied to enhance the patient’s self-efficacy and ability to act in difficult situations with other people. Patients are trained to notice that they can be in charge and actually change difficult situations. They learn how to shape situations differently to achieve new, changed outcomes for themselves.

The consolidation phase focuses on relapse prevention, reviews the therapy, and checks whether previously set goals have been achieved.

CBASP@YoungAge covers 20 to 30 sessions. Frequency is at least once a week and up to three times a week. It is up to the therapist to decide which modules to use and when based on the individual patient and her/his caregivers. After treatment completion, booster sessions can take place.

